#### Safety profile, ease of use, drug-drug interactions, intracellular half life

Both TDF and FTC have minimal side effects when used in HIV-infected subjects [31]. FTC and the closely related drug lamivudine are considered to be by far the most tolerable of current antiretrovirals [31]. TDF has been associated with renal dysfunction in some HIV-infected subjects, which is detailed further in section 3.3 and 3.4. Both drugs are formulated for once daily oral dosing as individual drugs and together as a combination fixed-dose single tablet for daily oral dosing (FTC/TDF). Neither drug has significant drug-drug interactions with non-antiretroviral drugs and neither interacts with hormonal contraceptives [31-33]. Both have long half-lives in plasma and peripheral blood mononuclear cells (PBMCs). FTC is phosphorylated by intracellular enzymes to its active form FTC 5'-triphosphate which has an intracellular half-life in PBMCs of 39 hours [34]. Tenofovir is also phosphorylated intracellularly to its active form tenofovir diphosphate which has an intracellular half-life in PBMCs of ≥60 hours [35]. In addition, tenofovir diphosphate inhibits HIV replication

in macrophages and other non-dividing cells, which may be important in preventing HIV infection in mucosal tissues.

*Mechanism of action, levels in genital tissues*

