#### **5.2.1 Duration of the Study**

Volunteers will be screened up to 42 days before randomization and will be followed for 6 months after the randomization.

It is anticipated that it will take approximately 3 months to enrol the study.

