#### **5.2.3 Inclusion Criteria for HIV-uninfected volunteers**

1. Healthy male or female, as assessed by a medical history and physical exam
2. At least 18 years of age on the day of screening and not older than 49 years on the day of randomization;

3. Willing to comply with the requirements of the protocol and available for follow-up for the planned duration of the study;
4. In the opinion of the Principal Investigator or designee, has understood the information provided and has provided written informed consent before any study-related procedures are performed;
5. Willing to undergo couple HIV testing, STI screening, HIV counseling and receive test results, and share results with partner
6. At risk for HIV infection as defined by at least one of the following: HIV-infected partner not using ART in the past 3 months and had episodes of unprotected vaginal sex with partner in the past 3 months
7. If a female of childbearing potential (i.e., not post-menopausal or surgically sterile), using an effective method of non-barrier contraception (hormonal contraceptive; intrauterine device (IUD); surgical sterility) from 7 days prior to randomization until the end of the study. All female volunteers must be willing to undergo urine pregnancy tests at time points as indicated in the Schedule of Procedures (Appendix A1).
8. HIV-infected partner is willing and eligible (see 5.2.5. and 5.2.6.) to enrol in the study

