## **6.7 Final Visit**

After stopping study drug at week 16 (see section 6.5), volunteers will have one additional follow-up visit at week 24, to assess for undetected HIV infection and immune responses once off study drug.

Research centre personnel will:

- Conduct HIV pre-test counselling or provide post-test counselling if the results of a prior HIV test are being provided to the volunteer.
- Collect blood and specimens for tests as specified in the Schedule of Procedures (Appendix A).
- Conduct HIV post-test counselling
- Provide HIV risk reduction counselling

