### **7.2 Medical History and Physical Examination**

At screening, a comprehensive medical history will be collected including history of sexually transmitted diseases and contraceptive practices.

A general physical examination includes the following: weight, height (at screening visit only), vital signs, and examination of skin, respiratory, cardiovascular, central nervous and abdominal systems, external ano-genitalia (screening only) and an assessment of cervical and axillary lymph nodes and.

During the screening period volunteers will be assessed for STI symptoms and provided or referred for appropriate management.

STI screening for males should include a history of STI symptoms, a genital exam, blood test for syphilis and collection of urine specimen for gonorrhoea and chlamydia testing.

STI screening for females should include a history of STI symptoms, an external genital exam, blood test for syphilis, collection of urine specimen for gonorrhoea and Chlamydia testing and collection of a vaginal swab for trichomonas, candida vaginitis and bacterial vaginosis testing.

At each study visit, an interim medical history and symptom directed physical examination will be performed. A symptom directed physical examination will include vital signs and any further examination indicated by history or observation.

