## **10.6 Pregnancy**

Although not considered an adverse event, if a female volunteer becomes pregnant during the study, it is the responsibility of the Principal Investigator or designee to report the pregnancy promptly to IAVI using the designated forms. However, serious complications of pregnancy that meet SAE criteria specified in the Section 10.4 of this Protocol (e.g., eclampsia, spontaneous abortion, etc.) should be reported as SAEs.

If a female volunteer becomes pregnant during the study, the administration of the investigational product will be discontinued and the volunteer followed until the end of pregnancy. Approximately 2–4 weeks after delivery, the baby will be examined by a physician to assess its health status and the results will be reported to IAVI.

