| Clinical Safety Assessments                                                                                                                                                                                                                          |        |       |     |     |       |            |        |       |           |       |             |           |           |
| Medical History including Concomitant Medications                                                                                                                                                                                                    | X      | X     | X   | X   | X     |            | X      | X     | X         |       | X           | X         |           |
| General Physical Exam****                                                                                                                                                                                                                            | X      |       |     |     |       |            |        |       | X         |       | X           |           |           |
| Directed Physical Exam *****                                                                                                                                                                                                                         |        | X     | X   | X   | X     |            | X      | X     |           |       |             | X         |           |
| Adverse Events/ Serious Adverse Events                                                                                                                                                                                                               |        | X     | X   | X   | X     |            | X      | X     | X         |       |             |           |           |
| Lab Samples                                                                                                                                                                                                                                          |        |       |     |     |       |            |        |       |           |       |             |           |           |

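### No adverse-event question or pregnancy test is scheduled after drug stops at Week 16, although volunteers return at Week 24, and the protocol disagrees with itself about history at that visit

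*Protocol*

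**What the plan says.** **When drug stops and follow-up ends.** Protocol Section 6.7: "After stopping study drug at week 16 (see section 6.5), volunteers will have one additional follow-up visit at week 24". Section 5.2.1 says volunteers "will be followed for 6 months after the randomization".

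**What Week 24 is for.** Section 6.7 gives the purpose as "to assess for undetected HIV infection and immune responses once off study drug". Its list holds HIV counselling and testing, the scheduled specimens and risk-reduction counselling.

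**What Appendix A1 schedules.** The row "Adverse Events/ Serious Adverse Events" is marked at Weeks 0, 1, 2, 4, 8, 12 and 16/ET. The pregnancy-test row is marked at screening and at Weeks 0, 4, 8, 12 and 16/ET. The medical-history row, which includes concomitant medications, runs from screening to Week 16/ET and reappears only at the two extra visits for HIV-infected volunteers. All three are blank at Week 24. Sections 9.1.1 and 9.7.4 tie adverse-event questioning and pregnancy testing to the Appendix A1 time points.

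**What other sections require.**
- Section 7.2: "At each study visit, an interim medical history and symptom directed physical examination will be performed".
- Section 9.1.2 asks for concomitant medications at every visit.
- Section 5.2.3, item 7, requires contraception "from 7 days prior to randomization until the end of the study".
- Section 10.6 requires prompt reporting, and follow-up to the end of pregnancy, "if a female volunteer becomes pregnant during the study".

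**The concern.** Safety is a primary objective, and the first primary endpoint is the proportion of volunteers with clinical adverse events of moderate or greater severity. Section 9.1.1 collects such events by an open question at scheduled visits. If that question is last asked on the day drug is stopped, an event that begins later is recorded only when someone volunteers it. The volunteer is nevertheless seen again eight weeks later.

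Drug is also still present after the last question. Section 3.1.4 says of the active form of emtricitabine "which has an intracellular half-life in PBMCs of 39 hours", and gives at least 60 hours for tenofovir diphosphate.

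Pregnancy raises the same problem. The protocol commits to following pregnancies through to an examination of the infant, but looks for none after Week 16. A conception shortly before that visit may be too early for its urine test.

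Section 5.1.1 sets no end to the observation period, and Section 14.2.1 tabulates events by time since randomization. A reader cannot tell whether the safety proportions describe 16 weeks or 24. An analysis plan could define the period later, but could not recover events that nobody asked about.

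**Working it through.** The protocol states no figure for this gap, so there is none to reproduce. The check sets the schedule against the text and does date arithmetic.

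**1. Is the blank at Week 24 real?** The HIV-test, drug-level and PBMC rows of Appendix A1 do carry a Week 24 mark. The blanks in the adverse-event, history and pregnancy rows are therefore not a column shift, and the Section 6.7 list agrees with them.

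**2. Text against schedule at Week 24.**

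| Item | Appendix A1 and 6.7 | Other sections | Result |
|---|---|---|---|
| AE/SAE question | absent | 9.1.1 defers to A1 | not scheduled |
| Pregnancy test | absent | 9.7.4 defers to A1; 5.2.3 item 7 and 10.6 run to the end of the study | not scheduled, though the obligations continue |
| Interim history | absent | 7.2: every study visit | contradiction |
| Symptom-directed examination | absent | 7.2: every study visit | contradiction |
| Concomitant medication | absent | 9.1.2: every visit | contradiction |

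In routine follow-up the directed-examination row is last marked at Week 12, because Week 16 has the general examination. Week 24 has neither.

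**3. Length of the interval.** Week 16 is day 112 and Week 24 is day 168.
- Nominal: 168 − 112 = 56 days; 56/168 = one third of follow-up.
- Windows: Week 16 is −7/+2 (days 105 to 114) and Week 24 is −7/+7 (days 161 to 175). Shortest gap: 161 − 114 = 47 days. Longest: 175 − 105 = 70 days.
- Person-time if all 72 volunteers reach Week 24: 72 × 56/365.25 = 11.0 person-years, of which 48 × 56/365.25 = 7.4 are in volunteers assigned to FTC/TDF.

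**4. Drug still present in that interval.** Five half-lives leave 1/32, about 3%, of the starting level.
- Emtricitabine triphosphate: 5 × 39 h = 195 h, about 8.1 days.
- Tenofovir diphosphate: 5 × at least 60 h = at least 300 h, or at least 12.5 days.
- For comparison, plasma tenofovir at 17 h (Section 3.3.3.2): 5 × 17 h = 85 h, about 3.5 days.

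**5. Routes that remain open after Week 16.** Unscheduled visits for illness may occur at any time (6.4). Serious events must be reported within 24 hours of awareness, with no Week 16 cut-off (10.4). Known adverse events continue to be followed (10.5). Pregnancies must be reported (10.6). The first, second and fourth depend on the event coming to notice, and the third covers only events already known.

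**The case against.** The strongest defence is that this is a design choice. In a 72-person pilot with 16 weeks on drug, Week 24 has an explicit and narrower purpose, and ending scheduled adverse-event questions at the end of treatment is defensible. That stands as far as it goes. It does not explain why Sections 7.2 and 9.1.2 require more than the schedule provides, or why pregnancy obligations outlast the tests that would trigger them.

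Several stronger readings are tempting, but the protocol does not support them:
- *Late events are lost altogether, so the off-drug period would look event-free.* The passive routes above contradict this. Serious events in particular are likely to surface. What is missing is scheduled solicitation, which matters most for non-serious moderate events.
- *The safety endpoints exclude off-drug time.* No section says so. Volunteers who stop drug early can also contribute off-drug time (7.12, 12.2).
- *History ends at Week 16.* Section 7.2 says otherwise, so for history the defect is a contradiction.
- *The six-month follow-up in 5.2.1 is contradicted.* It is not: volunteers are followed to Week 24, for a limited purpose.
- *A share of pregnancies going undetected can be calculated.* The protocol gives no detection lag, number of women or pregnancy rate, and effective non-barrier contraception is required of women of childbearing potential.
- *Liver flare after stopping goes unmonitored.* The flare warning in Section 3.3.1 concerns hepatitis B co-infection. HBsAg-positive volunteers are excluded (5.2.4), and Section 3.3.2 reports no transaminase difference after stopping among 56 women with chronic hepatitis B. No liver test is requested here.

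Residual intracellular drug also does not show that adverse events occur. It shows only that exposure continues past the last question.

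**Conclusion.** The point holds as a gap in solicitation and an internal contradiction. By Appendix A1 and Section 6.7, new adverse events and pregnancies are not systematically sought for 56 days (47 to 70 with visit windows), one third of planned follow-up. The first 8 to 12.5 or more days of that interval still carry intracellular drug, taking five half-lives as the yardstick. For history, directed examination and concomitant medication, the schedule and the text disagree, and the passages must be reconciled.

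How many events or pregnancies would go unrecorded cannot be estimated from the protocol. The pregnancy strand rests on the assumption that a very early conception may not yet give a positive urine test; no lag is quantified. No power or sample-size figure is affected. This is a modest but cheap improvement to a primary objective, and it has to be made before data collection because it cannot be made at analysis.

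**What to change.** 1. In Appendix A1, mark the adverse-event row, the medical-history row (with concomitant medications) and the urine pregnancy-test row at Week 24, and list the same items in Section 6.7.
2. Reconcile Section 7.2 with Appendix A1 and Section 6.7 on the symptom-directed examination at Week 24.
3. In Section 5.1.1 or 14.2.1, state the observation period, for example: *the AE and SAE endpoints count events from randomization to Week 24; on-drug and off-drug events are tabulated separately.*
4. In the same place, say how follow-up is counted for volunteers who do not attend Week 24. Section 12.2 excludes those whose drug was stopped for an adverse event, and Section 11.2.3 excludes those who become HIV-infected. Marking Week 24 does not reach them.

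The visit already takes place and blood is already drawn. The added cost is a few questions and one urine test per woman. The downside is that some extra unrelated adverse events will be recorded; the separate off-drug table keeps them from blurring the on-drug comparison.

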#### Renal toxicity of TDF in HIV-infected patients

TDF is generally well-tolerated; however the potential for renal toxicity has been suggested by case reports of proximal renal tubular dysfunction with or without a Fanconi-like syndrome in HIV-infected patients taking TDF. These cases had combinations of increased creatinine and decreased creatinine clearance, hypophosphatemia, proteinuria, and glycosuria without hyperglycemia starting from 5 to 16 months after starting TDF in combination with other antiretrovirals. In 11 of 13 cases

described, renal toxicity either improved or resolved after stopping the drug [48]. In a case series of 19 patients, the renal dysfunction appeared to be reversible and was associated with pre-existing renal insufficiency [49]. However, data from controlled clinical trials and cohort studies have shown little or no toxicity clearly associated with TDF in HIV-infected patients with normal baseline renal function. In 4 manufacturer-sponsored controlled clinical trials, there were no significant differences in renal abnormalities between the TDF and control groups over 44 weeks, 48 weeks, 96 weeks, and 144 weeks of therapy [50-55]. In the post marketing safety database and expanded access program for TDF, serious renal adverse events were observed in 0.5% of patients. Risk factors for development of renal toxicity were pre-existing renal dysfunction, concomitant nephrotoxic medications, low body weight, advanced age and low CD4 cell count [47]. Data from non-US, non-European populations also show low absolute rates of renal dysfunction in HIV-infected adults taking TDF. The Development of Antiretroviral Therapy in Africa (DART) trial, which enrolled 3314 antiretroviral naïve, HIV-infected adults in Africa, found that rates of severe renal impairment were low through 96 weeks of therapy and similar between TDF and non-TDF regimens. Sixty-five percent of patients were women [56]. A study of Thai HIV-infected patients on TDF found no significant changes in renal function through 21 weeks of therapy [57].

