These data show that the incidence of clinically significant renal dysfunction in HIV-infected patients taking TDF is likely to be very low. Current recommendations from the manufacturer and expert groups for TDF management in HIV-infected patients are: TDF dose reduction for patients with renal dysfunction (creatinine clearance  $\leq 50$  mL/min), avoidance of TDF co-administration with other nephrotoxic agents, and for patients with impaired creatinine clearance ( $\leq 90$  mL/min) twice yearly monitoring of renal function, serum phosphate, and urine protein and glucose [43, 58].

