## **7.8 Urine Collection**

Up to 50 mL of urine will be collected at the specified timepoints in the Schedule of Procedures (Appendix A1). All specimens will be handled according to the procedures specified in the Study Operations Manual. In the event of an abnormal laboratory value, volunteers may be asked to have an additional sample collected at the discretion of the principal investigator or designee.

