**9.1.3 Routine laboratory parameters**

Table 3 shows the laboratory parameters that will be measured routinely. These tests will include haematology and clinical chemistry. The samples for these tests will be collected at the time points indicated in the Schedule of Procedures (Appendix A1).

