**Table 3**  
**Laboratory Parameters**

| Laboratory Parameter | Test                                                                                                                                                |
|----------------------|-----------------------------------------------------------------------------------------------------------------------------------------------------|
| Haematology          | Full blood count (haemoglobin, leucocytes, platelets)
Differential count ( absolute neutrophil count, absolute lymphocyte count)                 |
| Clinical Chemistry   | Creatinine, creatinine clearance, serum phosphate,
Liver function tests: aspartate transferase (AST), alanine transferase (ALT), total bilirubin |

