#### **14.2.1 Safety and tolerability**

Adverse events will be classified according to the MedDRA body system and preferred terms. The number and percentage of subjects experiencing a given AE will be tabulated by treatment group, grade (severity/ relationship), and time since randomization.

Safety and tolerability will be assessed by examining the overall rates of adverse events and serious adverse events that are possibly, probably, or definitely associated with FTC/TDF. With 24 volunteers assigned to daily or intermittent FTC/TDF, observing no drug-related serious toxicity would result in an exact, two-sided, 95% confidence interval of (0.0000, 0.1425). If one drug-related SAE is observed, the exact, two-sided, 95% confidence interval would be (0.0011, 0.2112).

This study will have limited power to rule out all but very large relative increases in the risk of an adverse event due to FTC/TDF. For example, if 5% of the volunteers in the combined control group are expected to experience a given AE, this study has only 55% power to rule out a 10-fold increase (i.e., 5% vs. 50%) if there is no real increase. It has 63% power to rule-out a 15-fold increase (5% vs. 75%). For known FTC/TDF toxicities in HIV-infected persons, the observed AE rate among FTC/TDF recipients will be compared to historical data.

All clinical and routine laboratory data will be included in the safety analysis. Rate of study discontinuation and reasons for discontinuation will be determined by treatment group.

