| Hep BsAg and STI screening: urine for gonorrhoea and chlamydia; blood for syphilis; additionally for females vaginal swab for trichomonas, Candida vaginitis & bacterial vaginosis .
+ Swab to collect mucosal secretions for antibody secretion. | X      |       |     |     |       |            |        |       |           |       |             |           |           |
| Haematology (CBC) (+ plasma storage)                                                                                                                                                                                                                 | X      |       |     |     | X     |            | X      |       | X         |       | X           |           |           |
| Clinical Chemistry (creatinine, creatinine clearance, pancreatic amylase † , serum phosphate, aspartate transferase (AST), alanine transferase (ALT), total bilirubin                                                                     | X      |       |     |     | X     |            | X      |       | X         |       | X           |           |           |
| Urine dipstick +/- urinalysis                                                                                                                                                                                                                        | X      |       |     |     |       |            |        |       |           |       |             |           |           |
| HIV test                                                                                                                                                                                                                                             | X      | X     |     |     | X     |            | X      | X     | X         | X     | X**         | X**       |           |
| Pregnancy Test (all female volunteers)                                                                                                                                                                                                               | X      | X     |     |     | X     |            | X      | X     | X         |       |             |           |           |

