| LABORATORY                                                                  |                                                               |                                                               |                                                                 |                                                           |
|-----------------------------------------------------------------------------|---------------------------------------------------------------|---------------------------------------------------------------|-----------------------------------------------------------------|-----------------------------------------------------------|
| PARAMETER                                                                   | GRADE 1
MILD                                               | GRADE 2
MODERATE                                           | GRADE 3
SEVERE                                               | GRADE 4
POTENTIALLY
LIFE-THREATENING                |
| URINALYSIS Standard International Units are listed in italics |                                                               |                                                               |                                                                 |                                                           |
| Hematuria (microscopic)                                                     | 6 – 10 RBC/HPF                                                | > 10 RBC/HPF                                                  | Gross, with or without clots OR with RBC casts                  | Transfusion indicated                                     |
| Proteinuria, random collection                                              | 1 +                                                           | 2 – 3 +                                                       | 4 +                                                             | NA                                                        |
| Proteinuria, 24 hour collection                                             |                                                               |                                                               |                                                                 |                                                           |

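### The urine dipstick is scheduled at screening only, so urine signs of renal toxicity are not systematically observed on drug, although the primary renal endpoint counts toxicities from mild grade.

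*Protocol*

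**What the plan says.** The first primary safety endpoints (5.1.1) include the proportion of volunteers with renal toxicities of mild grade or worse. Other laboratory abnormalities count only from moderate grade. The renal tests that make up this endpoint are not listed.

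Section 3.3.1 describes TDF renal toxicity as combinations of raised creatinine or reduced clearance with "hypophosphatemia, proteinuria, and glycosuria without hyperglycemia". Its TDF adverse-reaction paragraph also lists urine glucose and haematuria among laboratory abnormalities seen in 2-12% of treated patients. Section 14.2.1 says that, for known FTC/TDF toxicities, "the observed AE rate among FTC/TDF recipients will be compared to historical data".

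Appendix B has graded rows for "Proteinuria, random collection" (1+ is Grade 1) and for microscopic haematuria. It has no row for glycosuria.

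On measurement, Appendix A1 has the row "Urine dipstick +/- urinalysis" with one mark, at screening. Section 7.8 adds no visit: "Up to 50 mL of urine will be collected at the specified timepoints in the Schedule of Procedures". Section 9.1.3 says of the routine tests that "These tests will include haematology and clinical chemistry", and the renal items in its Table 3 are "Creatinine, creatinine clearance, serum phosphate". Section 6.5, on the Week 16 or early termination visit, also defers to Appendix A1.

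**The concern.** The protocol makes the renal endpoint more sensitive than the other laboratory endpoints by counting Grade 1. It names two urine signs as part of the toxicity it is looking for, and section 5.2.4 uses the dipstick to exclude volunteers with abnormal urine. That gives a clean urine baseline, and the schedule never returns to it.

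What is at stake is how the renal result is read. A report of no renal toxicity would be taken to cover the tubular picture described in 3.3.1, while the urine part of that picture was not systematically looked for after the first dose. The historical comparison would likewise have no usable rate for urine glucose or haematuria. An analysis plan cannot repair this, because the data would not have been collected.

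**Working it through.** **1. What is measured on drug.** Reading Appendix A1 row by row, for the visits from randomization to Week 16:

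| Measure | Screening | Scheduled on drug |
|---|---|---|
| Creatinine, creatinine clearance, serum phosphate | yes | Weeks 4, 8, 16 |
| Urine dipstick or urinalysis (protein, glucose, blood) | yes | none |
| Urine pregnancy test, women only | yes | Weeks 4, 8, 12, 16 |

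The pregnancy test measures hCG and says nothing about protein, glucose or blood. The chemistry row is marked at later visits, so the gap is specific to urinalysis.

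**2. What the endpoint and comparison call for.**

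| Sign | Named in 3.3.1 as renal toxicity of TDF | Listed in 3.3.1 as a TDF laboratory abnormality | Graded in Appendix B | Scheduled on drug |
|---|---|---|---|---|
| Creatinine / clearance | yes | no | creatinine only | yes |
| Low phosphate | yes | no | yes | yes |
| Proteinuria | yes | no | yes, from dipstick 1+ | no |
| Glycosuria | yes | yes | no | no |
| Haematuria | no | yes | yes, by microscopy | no |

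Two of the four sign groups in the 3.3.1 description (creatinine/clearance and phosphate) are observed on drug. Proteinuria and glycosuria are not. The case for proteinuria rests on the endpoint and Appendix B. The case for glycosuria and haematuria in the historical comparison rests on the adverse-reaction list.

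**3. The protocol's precision figure and why it does not carry over.** Section 14.2.1 gives exact two-sided 95% intervals for n = 24, stated for serious drug-related toxicity. Both reproduce:

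- 0 of 24: upper limit = 1 - 0.025^(1/24) = 0.1425, so (0.0000, 0.1425).
- 1 of 24: (0.0011, 0.2112).

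These intervals assume that every volunteer was assessed. Suppose a urine abnormality is found only through for-cause testing, with probability s in those who have it. The chance of recording it is p × s, where p is the true proportion. With 0 of 24 recorded, the interval bounds p × s by 0.1425, so p ≤ 0.1425/s. At s = 1 this is the protocol's limit. At s of 0.1425 or less, the bound on p is 1 and the data exclude nothing. The documents do not give s.

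**4. Timing.** The renal cases in 3.3.1 began 5 to 16 months after TDF was started. Dosing here lasts 16 weeks: 16 × 7 = 112 days, about 3.7 months. On those reports few urine findings may arise during dosing. This lowers the expected yield of testing but leaves the mismatch between endpoint and schedule in place.

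**The case against.** The strongest reply is that the renal endpoint was always meant as a serum endpoint. Section 5.1.1 lists no components, section 3.5 says renal function is monitored by estimated creatinine clearance, and the specific renal rules in 12.1 concern creatinine and clearance. Appendix B is a generic grading table that 9.1.1 applies as a guideline, so a row there does not make a sign part of the endpoint. This stands as far as it goes: including proteinuria is a reading of 5.1.1 together with 3.3.1 and Appendix B, and the protocol does not state it outright. But neither 5.1.1 nor 14.2.1 is limited to serum tests, and if that was the intention they should say so.

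Section 14.2.1 also does not promise to measure every listed abnormality. Creatine kinase, triglycerides and cholesterol are not scheduled on drug either. That is fair, and it is a reason to state what the comparison covers.

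A reader might infer more than the documents support:

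- *That tubular toxicity cannot be seen, or that urine findings will be zero in every arm.* Phosphate and creatinine are measured on drug. Section 7.8 allows an extra urine sample after an abnormal value, 6.4 allows unscheduled visits, and 10.3 calls for indicated diagnostics when an event is assessed. Only systematic observation is missing.
- *That the trial falls short of the monitoring advice it cites.* That advice is "twice yearly monitoring of renal function, serum phosphate, and urine protein and glucose", for HIV-infected patients with clearance at or below 90 mL/min. Screening up to 42 days (6 weeks) before randomization plus 16 weeks of dosing is nominally at most 22 weeks, inside half a year. The documents also give no baseline clearance distribution.
- *That a number of missed cases can be computed from 2-12%.* That range is pooled over a list of abnormalities in HIV-infected patients on combination therapy. It gives no rate for any one urine sign, and 3.3.1 warns that such data may not represent uninfected persons.

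**Conclusion.** The mismatch is real and limited. The schedule provides no systematic on-drug observation of proteinuria, glycosuria or haematuria, while the endpoint text and the planned historical comparison are worded broadly enough to include them. A report with no urine findings would therefore not be evidence of their absence, and the (0.0000, 0.1425) interval could not be attached to them. The creatinine, clearance and phosphate results are unaffected.

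The conclusion rests on reading renal toxicities in 5.1.1 in the light of 3.3.1 and Appendix B, and on Appendix A1 being the complete schedule, as 6.5 and 7.8 indicate. Severity is minor to moderate: the yield of urine testing over 16 weeks may be low, no case count is supported, and the remedy may be a matter of wording alone.

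**What to change.** Reconcile the renal endpoint in 5.1.1, the historical comparison in 14.2.1 and the dipstick row in Appendix A1, by one of two routes.

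1. **Measure.** Repeat the screening dipstick at visits that already have chemistry (Weeks 4, 8 and 16, or at minimum Week 16) and report change from screening. Define how glycosuria is counted, since Appendix B does not grade it, and how a dipstick positive for blood is handled, since Appendix B grades haematuria by microscopy. The cost is one to three readings per volunteer with no new visit. Women already give urine at these visits, and men would give a spot sample. The downsides are some false positives, for example from menses, and the need to reconcile graded urine results with section 12.1, whose grade-based rules cover all laboratory values except creatinine elevations.
2. **Restate.** Define the renal endpoint as abnormalities of serum creatinine, creatinine clearance and serum phosphate, and state in 14.2.1 that the historical comparison excludes urine findings. This costs only wording, and the report would then claim no more than was measured.
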